#### Criteria for discontinuing or modifying allocated interventions {11b}

Each patient will be able to stop participating in intervention activities whenever they like. The activities within the PSG-meetings will be selected in agreement with the group members and will thus be tailored to their needs.

#### Strategies to improve adherence to interventions {11c}

The intervention is designed with the aim of making participation in the different intervention activities attractive. Moreover, patients will enjoy several services that they do not get outside the intervention, e.g. the browser-based web portal, the telephone-based health coaching and the patient feedback reports. Apart from this, no further measures will be undertaken to improve adherence. Any further measure would not be in line with the aim of performing a pragmatic randomised controlled trial. Attendance at the PSG-meetings will be documented by the PSG leaders, telephone calls will be documented by the telephone coaches, use of the digital components of the intervention will be documented electronically and delivery of the patient feedback reports will be documented by the Zi.

#### Relevant concomitant care permitted or prohibited during the trial {11d}

There are no restrictions on patients’ activities outside of or in addition to the intervention.

#### Provisions for post-trial care {30}

Participants will be encouraged to continue with the PSG meetings when the study is over. Trial participation is not expected to cause any harm that might require compensation.

### Outcomes {12}

#### 12.1 Outcomes

The primary outcome is defined as the number of hospital days within the last year prior to the end of the intervention. Hospital days include outpatient (e.g. emergency room or outpatient procedures) and inpatient benefits.

The secondary outcomes are the variables required for the testing of the secondary hypotheses (see the ‘Objective {7}’ section). These variables are:
Self-reported physical health assessed using an index based on the four physical health items of the EuroQol Questionnaire with 5 dimensions and 5 levels (EQ-5D-5L) [30]Self-reported physical activity assessed using a modification of the Godin Leisure Time Exercise Questionnaire (GLTEQ) [31]Self-reported nutritional behaviourIntention to follow the physical activity recommendation of the WHO [24] assessed using an item that has been self-constructed in line with usual practice when constructing items of this kind [32]Perceived behavioural control with regard to following the physical activity recommendation of the WHO assessed using an item that has been self-constructed in slight modification of the usual practice when constructing items of this kind [33]Intention to perform at least five of the nine items of health-promoting nutritional behaviour described in the questionnairePerceived behavioural control with regard to performing at least five of the nine items of health-promoting nutritional behaviour described in the questionnaireSelf-efficacy with regard to health-related self-management assessed using the 4-item short version [34] of the Perceived Medical Condition Self-Management Scale (PMCSMS) [35]Loneliness assessed using the 6-item short-version of the Revised University of California Los Angeles (UCLA) Loneliness Scale [36, 37]Depression assessed using the first two items of the Patient Health Questionnaire with 4 items (PHQ-4) [38]Anxiety assessed using the last two items of the PHQ-4 [38]

#### 12.2 Analysis metric

The analysis metric consists in changes from baseline.

#### 12.3 Method of aggregation

Data will be aggregated via statistical means.

#### 12.4 Time points

Hospital days will be sourced from the register data of the health insurance companies. These data are updated continuously. The collaborating health insurance companies will provide these data for evaluation after the intervention retrospectively to the point in time 1 year prior to the start of the intervention. The change scores for hospital days will be computed by subtracting the number of hospital days in the year directly before intervention start from the number of hospital days in the year directly before the end of the regular intervention, i.e. directly before month 18 after intervention start. Data for the secondary outcomes will be collected via a questionnaire (1) at enrolment (baseline survey), (2) 9 months after the start of the intervention (midterm survey), (3) 18 months after the start of the intervention (end survey) and (4) 27 months after the start of the intervention (follow-up survey). The baseline survey will be performed before the study participants have been informed about their assignment to one of the two study conditions. For the questionnaire variables, the core evaluation of the intervention will be based on the change scores between the values of the baseline survey and the values of the end survey, i.e. the survey at month 18 after intervention start.

#### 12.5 Explanations

The number of hospital days has been chosen as the primary outcome because hospital days constitute a major cost factor in the treatment of T2DM and CHD. A special outcome measure referring to possible physical harms of the intervention will not be applied because of the negligible probability of physical harms being caused by the intervention. However, each of the selected outcome measures can be used to detect negative effects of the intervention.

### Participant timeline {13}

The participant timeline is presented in Table 1.

**Table 1 Tab1:**
[figure not shown]
Participant timeline

### Sample size {14}

The most important analysis in the evaluation addresses the effect of the intervention on the primary outcome, i.e. the number of hospital days. As mentioned above, intervention and waiting control group will be compared with regard to the change scores of hospital days. These change scores will be computed by subtracting numbers of hospital stays 1 year before intervention start from numbers of hospital stays 1 year before the intervention end. The comparison of change scores will be performed using a *t*-test for independent samples. The sample size has been determined with regard to this test. The basic demand was that the test should be able to detect an effect of size 0.2 with a significance level of 0.05 and a power of 0.8. An effect size of 0.2 is a small effect according to Cohen [39]. However, unpublished analyses of our own with numbers of hospital days indicate that the standard deviation of change scores of hospital days will be between 5 and 10. In this case, an effect size of 0.2 would correspond to differences of one to two hospital days. Even a difference of only one day would mean a substantial difference in costs.

Further conditions presupposed for determining the sample are:
Two percent of the included persons could die during the intervention period or withdraw their consent for their data to be used.There could be a dropout rate of 15% in the intervention group and 20% in the waiting control group. The reason for this assumption is that up to 50% of the sample might consist of persons who are not ensured at AOK RH or BARMER. For these persons, the numbers of hospital days will not be provided directly by the health insurance companies. Instead, the patients will have to request the data from their health insurance companies and then transfer them to the project team. Several patients will not do this, with patients in the waiting control group being more likely not to do this. Within this sub-sample, a dropout rate of 30% in the intervention group and 40% in the waiting control group seems realistic. This would correspond to dropout rates of 15% and 20% in the total sample.The allocation ratio of intervention to control is 6:7.The sample size should be divisible by 13 because of the allocation ratio.

All these considerations imply a sample size of 1001.

### Recruitment {15}

The target population will consist of patients with T2DM and/or CHD. Recruitment will continue until end of June 2021 in six areas: the cities and surroundings of Aachen, Bonn, Cologne, Düsseldorf, Essen and Bünde. All these areas are located in North Rhine-Westphalia, the federal state with the largest population in Germany. Since this study will take place in an outpatient setting, several approaches to recruiting will be applied.

The main approach will rely on the collaboration of GPs. IGKE Cologne, AMED Aachen, IFAM Bonn, SAM Cologne, ifam Düsseldorf and IFAM Essen will contact the GPs of their research and teaching practice networks as well as those in their catchment areas via postal letter and telephone calls. GPs will be included depending on their willingness to recruit patients. Staff members of the recruiting institutions will visit the included GPs. During such a visit, the participating GP and the leading practice assistant will be informed about the details of the study, how to recruit patients, how to handle the study documents and other pertinent details. They will be asked to retrieve lists of eligible patients to facilitate recruitment during office hours. They will also be asked to encourage the participation of other GPs. The GPs will approach patients who fulfil the eligibility criteria (see Eligibility criteria {10}) for participation and obtain consent from those who agree to participate. From the patients recruited, the GPs will identify suitable patients willing to volunteer as PSG leaders. Patients will be recruited successively over a period of 6 months until end of June 2021. The GPs will receive 100 € per included patient. Moreover, they will be kept completely unburdened with study-related documentation.

In addition to the main approach, AOK RH and BARMER will send personalised letters to eligible patients and already recruited patients will be asked to encourage other patients to participate. In addition, already existing self-help groups will be contacted. All measures for recruiting patients will be accompanied by announcement of the P-SUP on the Internet, in local journals that feature health-related topics, and on local radio and local television. Patients approached via these routes will be asked to contact the P-SUP study coordinator. Members of the project team will then, together with the patient, contact the patient’s GP and try to get the GP to participate.

## Assignment of interventions: allocation

### Sequence generation {16a}

The randomisation will be stratified with regard to the six areas for which the participants have been recruited and with regard to the status of the participants, i.e. PSG leader versus common PSG member. Accordingly, there will be 12 different strata combinations. For each of these combinations, a specific allocation sequence will be applied. The first author of the protocol, who is also the chief evaluator of the project, will generate these sequences. The sequences will contain blocks to ensure that the actual distribution of intervention and waiting control patients in each strata combination is always close to the envisaged ratio of 6 to 7. Moreover, to ensure that assignments to the two study conditions cannot be predicted based on the preceding assignments, the assignments will be performed weekly and those parts of the allocation sequences applied for the respective week will be always brought into a new random order.

### Concealment mechanism {16b}

The allocation sequences will only be accessible to the person who has produced them. This person will assign the study conditions to the identification numbers of the newly recruited participants without having any information beyond these numbers and beyond information regarding the corresponding strata combinations. The assignment of a study condition to a specific participant will not be communicated to participants or to persons involved in their recruitment before the participant has returned the questionnaire of the baseline survey. Consequently, there will be a delay of at least 2 weeks between recruitment of a patient and the time when the assignment of that patient to a study condition is made public.

### Implementation {16c}

The GPs will obtain the consent of the participants and, at the same time, enrol the participants. Staff members of AMED Aachen, IFAM Bonn, SAM Cologne, ifam Düsseldorf and IFAM Essen will collect the signed consent form and the corresponding address data in the practices. The signed consent form and the corresponding address data will be transmitted to the IGKE Cologne. The IGKE Cologne will assign identification numbers to the address data and send the identification numbers to TRAc Bamberg. TRAc Bamberg will assign study conditions to the identification numbers and send the resulting assignments to the IGKE Cologne. The IGKE Cologne will inform the participants of their assigned study condition.

## Assignment of interventions: blinding

### Who will be blinded {17a}

Nobody will be blinded. This also applies to those persons who perform the central analyses for evaluation, because a reasonable blinding for these persons would not be feasible. For the primary outcome variable, this will be impossible because there will be more data sets for the waiting control group than for the intervention group. For this reason, the data analysts could identify the groups based on the numbers of data sets in both groups. Moreover, in addition to the intention-to-treat analysis, the data analysts will also perform a per-protocol analysis. For this analysis, the data sets of those members of the intervention group who have actually not participated in the intervention would have to be removed, whereas there would be no change for the waiting control group. For this reason, even if somebody other than the data analysts would prepare the data for the intention-to-treat and the per-protocol analysis, the data analysts could identify the study conditions by comparing the data sets for intention-to-treat and the per-protocol analysis. For the secondary outcome variables, blinding with regard to study conditions will be impossible, because the data analysts will also perform a process evaluation with data only from the intervention group and because data from the baseline survey will also be applied for this process evaluation.

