### Methods in analysis to handle protocol non-adherence and any statistical methods to handle missing data {20c}

In general, participants assigned to the intervention group will be free to avail themselves of the different intervention components or not. The extent to which they do so will be documented, and the relationship of the extent of such use to changes in primary and secondary outcomes will be analysed.

Missing data are only expected in the case of questionnaire data, i.e. for the secondary outcome variables. For the secondary outcome variables that are based on sum scores, missing values will be imputed by the means of those items belonging to the respective variable for which the participant has provided data. A participant who has no baseline value for a specific secondary outcome variable will be excluded from the analyses that refer to that particular variable. However, this participant will be included in all analyses that refer to the variables for which this participant has a value. An intention to treat analysis will be performed for all participants who have a baseline value. In this intention to treat analysis, missing end values will be imputed by taking into consideration the natural development that can be expected for the respective variable for the duration of the intervention. This natural development will be estimated by computing the differences between end and baseline values of the completers in the waiting control group. Accordingly, a missing end value for a particular variable will be estimated by adding the corresponding difference estimated from completers in the waiting control group to the baseline value. Should the resulting value exceed the measurement range of the respective variable, the missing value will be imputed by the range boundary that has been exceeded.

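### The per-protocol analysis removes non-participants from the intervention arm only, so its contrast is no longer protected by randomisation and can be biased in either direction

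*Protocol article*

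**What the plan says.** In the section Who will be blinded {17a}, the Protocol article states that "in addition to the intention-to-treat analysis, the data analysts will also perform a per-protocol analysis". The rule for the intervention arm is that "the data sets of those members of the intervention group who have actually not participated in the intervention would have to be removed". On the comparator side the same sentence foresees no removals at all: "whereas there would be no change for the waiting control group".

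Participation is the patient's own choice throughout. Section {11b} says "Each patient will be able to stop participating in intervention activities whenever they like". Section {20c} leaves the use of each component to the patient and adds that "the relationship of the extent of such use to changes in primary and secondary outcomes will be analysed".

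The outcome scale is set in section 12.2: "The analysis metric consists in changes from baseline". The only test stated for the primary outcome has no covariates: "The comparison of change scores will be performed using a *t*-test for independent samples" (Sample size {14}; repeated in substance in {20a}).

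The rule for judging effectiveness in {20a} uses that test and, if it is not significant, an analysis of variance of the secondary outcomes. It does not mention the per-protocol result.

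**The concern.** Whether an intervention patient takes part is known only after randomisation and depends on the patient. The control arm holds people who would also have stayed away, but nobody can tell who they are, so they all remain. The per-protocol contrast therefore sets a self-selected part of one arm against the whole of the other. Any difference in hospital-day change between joiners and non-joiners enters the estimate as if it were an effect of the programme. The stated test makes no adjustment for this.

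The extent-of-use analysis in {20c} shares the weakness. Groups meet weekly for 18 months and the outcome year is the last 12 of them, so illness in that year can reduce use as well as the reverse.

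At stake is how a supportive result is read. A per-protocol figure is easily taken as the effect in those who take part, and this one could differ from that effect by an unknown amount in an unknown direction.

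**Working it through.** **1. The plan's own figure.** Section {14} requires that "the test should be able to detect an effect of size 0.2 with a significance level of 0.05 and a power of 0.8". It gives 1001 patients, a 6:7 ratio, 2% death or withdrawal of consent, 15% and 20% dropout, and an SD of change of 5 to 10 days.
- Arms: 1001 × 6/13 = 462 intervention; 1001 × 7/13 = 539 control.
- Analysed: 462 × 0.98 × 0.85 = 384.8; 539 × 0.98 × 0.80 = 422.6.
- Power at 0.2 SD, two-sided 0.05: 0.809. The smallest multiple of 13 that reaches 80% is 988, so 1001 is reproduced to within 1.3%. Sidedness is not stated, but a one-sided test would need only 780.

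The sample size is not in dispute. It supplies the numbers analysed (385 and 423) and the scale: 0.2 SD is one to two days.

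**2. Shift caused by the deletion.** Change is final year minus baseline year, so a lower value is better. Let q be the share removed and g the mean change of those removed minus that of those kept.

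Mean of all = (1 − q) × kept + q × (kept + g) = kept + q × g, so kept = mean of all − q × g.

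With no true effect, the per-protocol difference is −q × g. It favours the intervention when g is positive and goes against it when g is negative. The article gives neither q nor g, so these are assumptions:

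| q | g (SD) | size of shift (SD) | days at SD 5 | days at SD 10 |
|---|---|---|---|---|
| any | 0 | 0 | 0 | 0 |
| 15% | ±0.3 | 0.045 | 0.225 | 0.45 |
| 30% | ±0.1 | 0.03 | 0.15 | 0.30 |
| 30% | ±0.2 | 0.06 | 0.30 | 0.60 |
| 30% | ±0.3 | 0.09 | 0.45 | 0.90 |

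The largest entry is 0.09/0.2 = 45% of the design effect.

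**3. Effect on the test at that extreme.** Kept: 385 × 0.70 = 269.5. Standard error: √(1/269.5 + 1/423) = 0.078 SD. Shift divided by standard error: 0.09/0.078 = 1.15. The chance of a significant result in favour with no effect is Φ(1.15 − 1.96) = 0.21, against a nominal 0.025. With g = −0.3 SD, the same 0.21 applies against the intervention.

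**4. Direction.** Hospital-day counts were simulated with no effect, 385 against 423 patients, about 30% of the intervention arm removed, an SD of change of about 10.4 days, and 2000 trials per mechanism.

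| Who tends not to take part | Mean per-protocol difference (days) | Rejections | Of all trials, rejections in favour | Intention-to-treat rejections |
|---|---|---|---|---|
| Many hospital days in follow-up | −0.71 (towards benefit) | 14.1% | 13.9% | 4.5% |
| Many hospital days at baseline | +0.73 (against) | 15.6% | 0.1% | 5.4% |
| Stably frail | about 0 | 4.2% | 2.2% | 4.9% |

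The sign depends on the mechanism because the outcome is a change. Removing patients with high baseline use removes those who would have regressed towards the mean. A stable difference in level largely cancels. Comparing the arms as randomised keeps the error rate near 5% in all three cases.

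**5. The alternative.** The complier average causal effect is the intention-to-treat difference divided by (1 − q). With no effect, its numerator is centred on zero whatever g is. Its standard error is about √(1/385 + 1/423)/(1 − q): 0.070/0.85 = 0.083 SD at q = 15% and 0.070/0.70 = 0.101 SD at q = 30%. The latter compares with 0.078 SD for the deletion in step 3.

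**The case against.** The strongest defence is that no conclusion of the trial depends on this analysis. It is additional to intention-to-treat and plays no part in the effectiveness rule. That stands, and it limits the weight of the point.

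It can also be said that the rule appears only as an argument about blinding, in the conditional, and that the full definition may be in a statistical analysis plan that is not shown. This stands for the participation threshold and any adjustment, whose absence is not criticised here. It does not cover the population itself, because the article commits to the analysis and says which arm loses patients. Controls have no programme to decline before month 18, so one-sided removal is the usual form of per-protocol in such a design. That explains the rule but does not restore comparability.

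A reader might infer that the rule builds in a bias towards benefit, because non-attenders are sicker or because a patient in hospital cannot attend. The documents do not support that. Sicker is a difference in level, which largely cancels in a change score, and high baseline use pushes the other way. Read literally, the rule removes those who did not take part, and a hospital stay late in the programme does not make an earlier participant a non-participant.

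Nor do the documents give a participation rate. The 15% and 30% for the intervention group in {14} concern hospital data that are not supplied, and the q range used here is not taken from them.

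**Conclusion.** The point holds as a weakness of a supportive analysis. The stated per-protocol rule selects one arm on voluntary behaviour after randomisation and leaves the other whole, so its estimate can be shifted in either direction. Under assumed q of 15% to 30% and g of −0.3 to +0.3 SD, the shift runs from −0.09 to +0.09 SD, that is up to 0.45 days at an SD of 5 and 0.9 days at an SD of 10. It is zero if joiners and non-joiners change alike. Bias towards benefit is plausible if illness during follow-up drives non-participation, but nothing in the article establishes it. The sample size, the intention-to-treat comparison and the decision rule in {20a} are untouched. The change is worth making because a comparison that keeps both arms as randomised is available from records the trial already plans to keep.

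**What to change.** - Replace the one-sided deletion with a complier average causal effect that keeps both arms as randomised and uses assignment as the instrument (two-stage least squares, for example), or report this beside it as the main supportive estimate. Controls receive the programme only after month 18, so non-compliance is one-sided.
- Define non-participation in advance as no recorded use of any active component: group meetings, coaching calls or portal. Section {11c} already provides for these records. A minimum-use threshold would be worse, because patients below it may still have gained something, and that breaks the exclusion assumption.
- State that assumption: assignment does nothing for patients who use no active component. Note that feedback reports forwarded by the GP may reach such patients, so it may not hold exactly.
- Label any per-protocol result that remains as supportive and open to selection bias of unknown direction.
- Label the extent-of-use analysis in {20c} as descriptive. A single binary instrument cannot identify a dose-response relationship without assuming linearity.

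The cost is some analysis-plan wording and one small analysis. The sample size does not change. The downside is a wider interval, by a factor of about 1/(1 − q) over intention-to-treat (1.18 at q = 15%, 1.43 at q = 30%), and reliance on the exclusion assumption.
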